## Abstract

**Background:**

Telemonitoring technology offers one of the most promising alternatives for the provision of health care services at the patient's home. The primary aim of this study is to evaluate the impact of a primary care-based telemonitoring intervention on the frequency of hospital admissions.

**Methods/design:**

A primary care-based randomised controlled trial will be carried out to assess the impact of a telemonitoring intervention aimed at home care patients with heart failure (HF) and/or chronic lung disease (CLD). The results will be compared with those obtained with standard health care practice. The duration of the study will be of one year. Sixty patients will be recruited for the study. In-home patients, diagnosed with HF and/or CLD, aged 14 or above and with two or more hospital admissions in the previous year will be eligible.

For the intervention group, telemonitoring will consist of daily patient self-measurements of respiratory-rate, heart-rate, blood pressure, oxygen saturation, weight and body temperature. Additionally, the patients will complete a qualitative symptom questionnaire daily using the telemonitoring system. Routine telephone contacts will be conducted every fortnight and additional telephone contacts will be carried out if the data received at the primary care centre are out of the established limits. The control group will receive usual care. The primary outcome measure is the number of hospital admissions due to any cause that occurred in a period of 12 months post-randomisation. The secondary outcome measures are: duration of hospital stay, hospital admissions due to HF or CLD, mortality rate, use of health care resources, quality of life, cost-effectiveness, compliance and patient and health care professional satisfaction with the new technology.

**Discussion:**

The results of this study will shed some light on the effects of telemonitoring for the follow-up and management of chronic patients from a primary care setting. The study may contribute to enhance the understanding of alternative modes of health care provision for medically unstable elderly patients, who bear a high degree of physical and functional deterioration.

**Trial Registration:**

ISRCTN: ISRCTN89041993

## Background

It is estimated that by 2020, chronic diseases will contribute to more than 60% of illnesses requiring treatment [1]. Frequently, several chronic diseases occur at the same time in the same patients, often elderly individuals. This patient group, progressively growing in size, is characterised by a high use of health care resources, elevated rates of hospitalisations and a high prevalence of disability and dependence during the course of the disease [1-4]. Elderly chronic patients frequently experience multiple hospital admissions and such exacerbations have a major impact on the quality of life. There is good evidence that early identification of the exacerbations that arise from heart failure (HF) and chronic lung disease (CLD) reduces the risk for hospital admission and improves the quality of life of these chronic patients [5,6].

In the view of the ageing population and the growing impact of chronic diseases, there is a pressing need to adapt and to search for new approaches to health care. In this sense, the used of information and communication technology (ICT) applied to the monitoring of chronic patients provides new health care alternatives. Thus, novel methods for the delivery of quality health care could increase the effectiveness of chronic disease management while containing costs and using scarce human resources to maximum effect. Home telemonitoring allows the transmission of patients' vital signs once or more per day and provides diagnostic information to health care professionals. Telemetric-supported self-monitoring of HF and CLD has the potential to promote self-care, improve compliance, enable timely response to deterioration and improve the follow-up after hospital discharge [7,8]. A number of studies have shown that telemonitoring improves the quality of life of patients and their families [9,10]. From an economic view point, home telemonitoring of chronic patients appears to reduce health care costs [11-14]. Nevertheless, higher-quality economic studies are required to give greater insights into the potential cost-effectiveness of home telemonitoring [15].

Home telemonitoring has been found to reduce rates of hospitalisation and emergency department visits for chronic obstructive pulmonary disease (COPD) patients, while findings for hospital bed days were not consistent and varied between studies [15,16]. There was a higher mortality-rate among patients with COPD using home telemonitoring compared with usual care, but the number of original studies was scarce and the sample sizes were relatively small. Hence, the outcomes must be interpreted cautiously [15,16]. According to recent systematic reviews, telemonitoring interventions for patients with HF have been shown to be effective in reducing the risk of all-cause mortality, HF-related hospitalisations and emergency department visits [15,17-19]. Moreover, the use of home telemonitoring for patients with HF improved quality of life, patient self-care and evidence-based prescribing [15,17-19]. However, further studies of high methodological quality are required to give more precise information about the potential clinical benefits of home telehealth interventions prior to scaling-up the use of the new technology [7,19].

The telemonitoring system used in the present study is based on a telemonitoring system employed in another hospital-based clinical trial [20]. The home telemonitoring system has been successfully tested on patients with HF and COPD in a randomised controlled trial carried out in Donostia University Hospital (Basque Country), *Current Controlled Trials *ISRCTN62033748. In contrast to the aforementioned trial, in the present study the management of the telemonitoring intervention is carried out by primary care nurses and general practitioners (GPs). To the best of our knowledge, no other primary care-based tele-homecare studies have been undertaken with regards to the type of patients and the telemonitoring procedure employed in this investigation.

### Hypothesis and objectives of the study

The hypothesis that we set out to test in this study is that telemonitoring controlled by a primary care team can benefit home care patients with HF and/or CLD, and thereby, reduce the number of hospital admissions. We also postulate that home telemonitoring may improve the quality of life of these patients in a way that is cost-effective and acceptable to both, patients and health care professionals.

The **main objective of the study **is to evaluate the impact of a primary care-based telemonitoring intervention on the use of health care resources, specifically on the frequency of hospital admissions.

The **secondary objectives **are:

1. To analyse the impact of the intervention on mortality, duration of hospital stay, use of emergency services, visits to primary care physicians and to specialists, home visits, and telephone calls.

2. To evaluate the telemonitoring procedure in economic terms compared to usual care through a cost-effectiveness analysis. The impact on the quality of life of the participating patients will also be assessed.

3. To assess the degree of satisfaction of the patients/caregivers and health care professionals with the telemonitoring intervention.

## Methods/design

### Main characteristics of the study

#### Study design

This is a randomised controlled trial with a one-year follow-up. In the intervention group (IG), in addition to the standard practice, patients will be monitored using a telemonitoring procedure, while the control group (CG) will receive the usual care. Participants will gradually join the study over a period of six months. The recruitment period could be extended to reach the targeted number of patients. Interim data analysis will be carried out after 3 and 6 months of follow-up and the final results will be obtained at 12 months post-randomisation. Figure 1 outlines the general study design.

**Figure 1 F1:**
[figure not shown]
**General design of the randomised controlled trial**.

#### Study area

This study is being carried out across 23 health centres of the Bilbao Primary Care Health Region (Basque Country, Spain). The Health Region serves a catchment population of 390,000 people, of whom around 27% are over 60 years old. The team of professionals in charge of the first level of health care is composed of 218 GPs, 269 nurses and 44 paediatricians. At the hospital level, there are two public referral centres: Basurto Hospital, the main hospital in the area, and Santa Marina Hospital, which is primarily focused on chronic diseases and palliative care.

### Intervention

#### Description of the intervention

In the IG, telemonitoring will consist of daily transfers of the following self-measured clinical parameters: respiratory-rate, heart-rate, blood pressure, blood oxygen saturation using pulse oxymetry, weight and body temperature. Together with the clinical data, patients will also complete a brief questionnaire aimed at assessing the patient's perception of his/her medical and functional condition. The questionnaire also contains items concerning compliance with medication and diet. Health professionals will check the data daily and will routinely contact the patient by phone every two weeks (nursing staff). Other telephone contacts will be carried out, if necessary, if the data received at the primary health care centre are out of the established limits. The telemonitoring system comprises personalised alerts set for each patient, with messages being sent to a Web-based platform when the recorded parameters fall outside established limits (which may be adjusted over time).

We have established standard initial threshold values for all the telemonitored parameters, which can be further modified by health care professionals according to the specific characteristics of the patients. The established threshold values are essential for the monitoring of the patient's condition and for the detection of unusual changes. When the measurements fall outside the established limits, alerts will be triggered via the PDA terminal and the clinical staff will act according to the medical condition of the patient. Alternatively, the patients will be advised to call the emergency services at the weekends and at times when the health centres are closed.

The standard threshold values for alerts are shown in Table 1.

**Table 1 T1:** Established thresholds for the telemonitored parameters.

Telemonitored parameters	Established threshold values
Respiratory-rate	< 12 or >24 breaths per minute (bpm)
Heart-rate	< 50 or >100 beats per minute (bpm)
Systolic blood pressure	< 100 or >160 millimeters of mercury (mmHg)
Diastolic blood pressure,	< 60 or >95 millimeters of mercury (mmHg)
Oxygen saturation	< 95% (this is a frequently adjusted limit for patients with CLD)
Temperature	> 37°C
Weight	Should be notified if there is an increase of 1 Kg in three days
Qualitative questionnaire	Negative answers to the questionnaire which correspond to: feeling worse, breathing difficulties, increased nocturia, oedema, worsening of cough, increased sputum production and a change in sputum colour

In the CG, patients will receive usual care, consisting of regular medical examinations in line with the established programmes for monitoring home-based patients. The frequency of the medical examinations will vary depending on the clinical, social and family situation of each patient. Additionally, the GP and/or nurse will see or call the patient on demand in the event of a deterioration in the medical condition. Note that the IG will receive usual care, as well as the extra telemonitoring specified under the study protocol.

Prior to the intervention, all GPs and nurses in charge of the care of the participating patients (in both IG and CG) will attend a 4-hour workshop on the management of HF and COPD and early detection of relapses. Additionally, the health care professionals involved with the IG will receive further training on the use of the telemonitoring system. The key activities for the CG and IG are outlined in Figure 2.

**Figure 2 F2:**
[figure not shown]
**Key activities for the intervention (IG) and control (CG) groups and personnel involved in the study**.

#### Technical features of the system and devices for data transfer and reception

The telemonitoring equipment, supplied by Saludnova [20], consists of a touch screen PDA which runs the Microsoft's Windows Mobile operating system, with wireless Bluetooth sensors to measure blood pressure, heart-rate and oxygen saturation, and manual input of body temperature, respiratory-rate, weight, questionnaires on the medical condition, any perceived changes and a record of compliance with medication and diet. The telemonitoring kit used by patients in the intervention group is shown in Figure 3. The data will be transferred via GPRS to the Web-based platform (Web data manager). The centralised Web management system allows different levels of access depending on the specific roles of the participating professionals (project leaders, GPs/nurses, hospital). The screen of the Web-platform accessed by health care professionals to check the transmitted data is shown in Figure 4. Although the platform can be accessed from any computer connected to the internet, it should be noted that there are terminals available in the consultation rooms of the health centres and in one of the referral hospitals (Santa Marina Hospital), which given its characteristics, often provides care to this type of patients.

**Figure 3 F3:**
[figure not shown]
**Telemonitoring kit used by patients in the intervention group**.

**Figure 4 F4:**
[figure not shown]
**Web-platform accessed by health care professionals**.

### Study Population

#### Eligible patients

The patients included in the study are all attached to the health centres of the Bilbao Primary Health Care Region, are under home care (*i.e*.: in-home patients that receive routine health care at home due to lack of or severe difficulties with mobility), aged 14 or above, have been diagnosed with HF and/or CLD, with two or more hospital admissions during the previous year and at least one of these admissions having been associated with one of the two conditions under study.

#### Exclusion criteria

The following patients are excluded from the study: those in residential care under the supervision of specific health care professionals, those receiving regular monitoring or treatment by specialists or hospital services (such as, rehabilitation programmes, haemodialysis, care in hospital day-care centres, etc.), those in the terminal phases (with a life expectancy under 6 months) of other illnesses (not HF or CLD), patients with cognitive impairment and those not willing to participate in the study.

#### Patient selection process

The lists of patients with two or more hospital admissions for any cause between the 1^st ^of December 2008 and the 1^st ^of December 2009 (12,293 people) was obtained from the hospital records of the two referral hospitals of the Health Region. Subsequently, 240 in-home patients suffering from the clinical conditions under investigation (*i.e*.: HF and/or CLD) were identified using the primary care medical record database ("Osabide"). Fifty nine of these home care patients met all the inclusion criteria and constituted the group of potentially eligible participants for the first phase of the recruitment process. One of the limiting inclusion criterion applied was the fact that at least one of the hospital admissions had to be due to HF or CLD. Progressively, inclusion of additional patients will also be sought through meetings held in the health centres, until the pre-established number of patients is reached.

#### Randomisation

We used a stratified random sampling by disease (HF, CLD or both), which consisted of the random selection of patients for allocation to the control and intervention groups from three containers holding the codes of the initial patients. Subsequent draws were made to maintain the 1:1 ratio between the two study groups and between the three different strata considered.

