#### Recruitment of patients

After GPs and nurses from the 23 health centres agreed to join the study, eligible patients were provided with information about the study and were invited to participate and sign a written informed consent form. Additionally, the patients from the IG were given a "Patient information sheet" with detailed information concerning the telemonitoring intervention.

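### The text reads most naturally as drawing arms before consent, with the arm apparent at recruitment; the order and the rule for later draws should be stated, and remaining patients should consent before a concealed allocation.

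*Protocol article*

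**What the plan says.** All references are to the protocol article.

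- **Patient selection process.** Hospital and primary care records yielded 59 home care patients who met the inclusion criteria. They "constituted the group of potentially eligible participants for the first phase of the recruitment process". Nothing says they had consented. For later entrants: "Progressively, inclusion of additional patients will also be sought through meetings held in the health centres".
- **Randomisation.** Allocation is stratified by HF, CLD or both. It is described as "random selection of patients for allocation to the control and intervention groups from three containers holding the codes of the initial patients", followed by: "Subsequent draws were made to maintain the 1:1 ratio between the two study groups", and likewise across the three strata.
- **Recruitment of patients.** Eligible patients were informed, invited and asked to sign consent. The section continues: "Additionally, the patients from the IG were given a" separate sheet describing telemonitoring.
- **Exclusion criteria.** People unwilling to take part are excluded.
- **Primary outcome measure.** Admissions are counted over 12 months from randomisation.
- **Study design.** "Participants will gradually join the study over a period of six months".
- **Ethics approval.** Written consent came before participation. Its position relative to randomisation is not given.
- **Secondary outcome measures, closing paragraph.** Eligible people who declined, and their reasons, will be recorded. No breakdown by arm is mentioned.
- **Study limitations.** Neither participants nor treating professionals can be blinded.

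**The concern.** Randomisation makes groups comparable only for the people who were randomised. If patients learn their arm and then decide whether to join, and those who refuse leave the trial, the groups analysed are those who accepted their assigned arm.

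The two arms ask very different things here. The IG takes daily self-measurements and answers a questionnaire on a handheld device, while the control group (CG) continues with usual care. Housebound patients who are frailer, or uneasy with the device, could decline the IG and yet accept usual care. If such patients would have had more admissions, the IG would look better with no treatment effect.

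A second consequence concerns time. If the draw precedes consent, a count that starts at randomisation includes time before the patient was enrolled and, in the IG, before telemonitoring could begin.

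**Working it through.** **Step 1: reading the sections together.** Three facts point to a draw before consent.

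1. The draw used codes of the initial patients. The only initial group described is the list of 59 identified from records.
2. At recruitment, where patients are informed and invited, an IG already exists and has its own sheet.
3. Unwilling patients are excluded, so a refuser after the draw would leave the trial.

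The consent statement under Ethics approval fits either order. The first-phase list (59) is almost as long as the recruitment target (60), so if the inference is right, much of the sample could be affected. How many of the 59 consented is not given.

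**Step 2: the plan's own power figure.** Inputs from Sample size: CG mean 3.5, SD 1.7, 35% reduction, 30 per arm, 10% loss, 5% level (taken as two-sided).

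- Assumed effect: 0.35 × 3.5 = 1.225 admissions.
- Analysed per arm: 30 × 0.9 = 27.
- Two-sample t-test power: 73.8%. With the Mann-Whitney efficiency of 0.955: 71.8%. The stated 72% is reproduced. It neither supports nor weakens this point, but it supplies the scale for Step 3.

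**Step 3: how large could arm-dependent refusal be?** The document gives no refusal rates, so the inputs are assumptions shown over a range.

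- r = share of IG-assigned patients who refuse (10%, 20%, 30%), with no refusal in the CG.
- k = excess mean admissions of refusers over consenters (0.5 to 1.7, the upper end being one planned SD).
- The overall mean equals the consenters' mean + r × k, so the IG consenters' mean falls below the CG mean by b = r × k with no treatment effect.
- Standard error with 27 analysed per arm: 1.7 × √(2/27) = 0.463.
- Two-sided type I error (normal approximation): Φ(b/0.463 − 1.96) + Φ(−b/0.463 − 1.96).

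| r | k | b = r × k | b / 1.225 | Type I error |
|---|---|---|---|---|
| 10% | 0.5 | 0.05 | 4% | 5.1% |
| 10% | 1.7 | 0.17 | 14% | 6.6% |
| 20% | 0.5 | 0.10 | 8% | 5.5% |
| 20% | 1.7 | 0.34 | 28% | 11.4% |
| 30% | 0.5 | 0.15 | 12% | 6.2% |
| 30% | 1.7 | 0.51 | 42% | 19.7% |

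If refusers had fewer admissions than consenters, the shift would have the same size in the other direction.

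**The case against.** The strongest reply is that the order is inferred. Sections of an article need not be chronological, and the IG sheet could have been handed over after signature. That stands, which is why the order is put here as the natural reading and not as a fact. No sentence supports the rival order either.

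A reader might infer more than the text supports:

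- **That allocation was unconcealed.** Drawing coded identifiers from containers can be concealed. Who drew, and how arms were withheld, is not described, and an article may leave that to the full protocol.
- **That balance was forced, or refusers replaced.** The text speaks of maintaining 1:1. Later draws may simply allocate later entrants within strata, which is ordinary restricted randomisation. Replacement of refusers is not mentioned.
- **That staff could predict the next arm.** Sixty patients over 23 centres is about 2.6 per centre, split over three strata. Prediction would require knowing draws made elsewhere, which nothing in the text says.
- **That delay between draw and start costs a stated amount of power.** Gradual entry does not show that patients were drawn long before they joined. No interval is given, so no figure can be attached.

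The plan also has partial safeguards. It records decliners and their reasons, collects severity where available to check comparability, compares baseline characteristics, and adjusts where they differ significantly. These help, but significance tests with about 30 per arm can miss imbalances that matter, and adjustment cannot reach unmeasured reasons for refusing.

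**Conclusion.** The point holds as a weakness in the described sequence, not as a demonstrated bias. Read together, the sections on selection, randomisation, recruitment and exclusion most naturally describe arms drawn from patients who had not yet consented, with the arm apparent at recruitment. The article neither states the order nor gives the rule for later draws. As described, the sequence permits refusal to depend on arm in an unblinded trial, and it would start the primary count before enrolment.

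The size is unknown. Under the assumed range, the effect runs from negligible (0.05 admissions, type I error 5.1%) to serious (0.51 admissions, 19.7%). This rests on refusal in the IG only, refusers having more admissions, and 27 patients analysed in each arm. If consent in fact came before the draw, this bias does not arise and a clarifying sentence is enough. Otherwise the change for remaining patients is a cheap improvement that cannot be made once enrolment closes.

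**What to change.** **Patients still to be enrolled.** Obtain consent and baseline data first. Then allocate within the HF, CLD and both strata from a concealed sequence held by someone outside the health centres. Start the 12-month count on the allocation date.

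**Patients already drawn.**

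- State whether consent came before or after the draw, and the rule for later draws.
- Report by arm the numbers drawn, consenting and refusing, with reasons. Decliners and reasons are already to be recorded, so the addition is the split by arm.
- Compare the available baseline data of consenters by arm.
- If refusal differed by arm, present it as a limit on the conclusion.

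An analysis of everyone by the arm first drawn is not proposed, because it would need outcomes on people who did not consent.

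**Cost.** A short amendment, a small logistic step per patient, and possibly slightly unequal arm sizes.
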